### Charlson Co-morbidity Index

*A medical professional assessment of patients' expected co-morbidities* Charlson Co-morbidity Index is a validated method for calculating co-morbidity for each patient
[33,34]. The information contained in the co-morbidity calculation is retrieved from the National Patient Registry. The Charlson Co-morbidity Index is divided into three parts where the first part is patients who are not registered in the National Patient Registry and have no co-morbidity (point 0); the second part is patients who are registered with mild to moderate co-morbidity (1–2 point) and the third part is patients who are those with severe co-morbidity
[35]. It would be atypical if the study population is a heterogeneous group of patients, but the co-morbidity can be a way of making the study population more heterogeneous. The Charlson Co-morbidity Index has in other Danish and international studies proved to be an important confounder that should be adjusted for, or used as a predictor
[36-38].

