#### Population

Patients scheduled for a total hip arthroplasty (THA).

This group represents a part of the adult population suffering from chronic pain. It has been shown that five to ten percent of these patients suffer from severe chronic pain postoperatively
[39].

Patients scheduled for a shoulder-operation.

This group was chosen because it constitutes a group of younger patients suffering from pain. Previously, they have been identified as a group who tend to develop anxiety and concern
[17].

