#### Inclusion criteria

All hip- and shoulder-patients who are referred for the first time to the Department of Orthopaedic Surgery at Kolding Hospital, a part of Lillebaelt Hospital and the Department of Orthopaedics and Traumatology, Odense University Hospital, Denmark are included. The patients must be able to speak and read Danish and must be at least 18 years old. To be included, they must enter a patient programme that implies an operation.

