#### Exclusion criteria

Patients with primary and secondary bone tumour or who are registered as terminal are excluded. Patients who have experienced a trauma against the shoulder within the past four weeks and those diagnosed with severe mental disorders such as schizophrenia, paranoid psychosis and bipolar affective disorders are excluded.

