### Study variables

The analysis will be done by CMD-SQ, EQ-5D, HVOK, SF-12, RCS, OHS/OSS and the Charlson Index. Besides, social demographic data such as gender, age, weight, height, citizenship, civil status and educational level will be included.

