## Discussion

The use of preoperative evaluation of patient anxiety and concern has not been done routinely in shoulder and hip surgery. This study aims to investigate the correlation between patient anxiety and concern and postoperative outcome. The hypothesis is that anxious and concerned patients are less satisfied with their treatment and have a poorer overall outcome of their treatment. If it is possible to confirm this hypothesis, it will be recommended to screen all hip- and shoulder-patients for anxiety and concern preoperatively. This will make it possible to optimize patient information, and to select patients with the likelihood of having a good patient reported outcome postoperatively.

The study is dependent on the fact that all patients fill in the questionnaire four times, and for that reason the study can be challenged by dropouts. Therefore, in order to get 202 patients (i.e. the required sample size) it is planned to include 250 patients. Experiences from other studies using the same versions of the PRO questionnaires have shown close to a 90 percent response rate which makes our patient number sufficient as planned in the power calculation
[6,43].

It is decided to send the questionnaire to the patients 12 and 52 weeks after the operation as it has been shown that these periods constitutes stable periods for patients functional ability and pain in their recovery after the operation
[44-47]. It is important to measure the patients when they are in a stable period because otherwise the outcome will be biased.

We have included the test-retest reliability of the CMD-SQ as this is recommended for each screening of a new population in a new context. The outcome of a reliability test, in this case a questionnaire, is a result of the data from this specific measurement in this specific patient group and not a result of the questionnaire itself
[42]. Therefore the result of the reliability test of CMD-SQ in this study can be compared to the results of other reliability tests of CMD-SQ, but it can not be used directly in a different population.

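### Shoulder patients enter with unspecified operations, but operation type is not among the planned confounders, so the shoulder CMD-SQ coefficient may partly reflect case mix

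*Protocol article*

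**What the plan says.** All references are to the Protocol article.

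- **Population.** The hip group is defined by a single procedure, total hip arthroplasty. The other group is "Patients scheduled for a shoulder-operation", with no procedure or indication.
- **Inclusion criteria.** The requirement on surgery is general: "To be included, they must enter a patient programme that implies an operation".
- **Exclusion criteria.** Four clinical limits apply: bone tumour, terminal status, recent trauma ("Patients who have experienced a trauma against the shoulder within the past four weeks") and severe mental disorder. None selects a type of shoulder operation.
- **Study variables.** "The analysis will be done by CMD-SQ, EQ-5D, HVOK, SF-12, RCS, OHS/OSS and the Charlson Index", followed by sociodemographic data. Neither operation nor indication is named.
- **Statistical analysis.** Multiple linear regression is run from baseline to 12 weeks and from baseline to 52 weeks. Confounding is to be examined with the Charlson Index and sociodemographic data, and the latter are itemised after *i.e.* (sex, age, weight, height, citizenship, civil status, education). The analyses are to be done separately, but the text does not say whether this means by joint or by questionnaire.
- **Charlson Co-morbidity Index.** "It would be atypical if the study population is a heterogeneous group of patients", after which co-morbidity is offered as a means of making the population more heterogeneous.

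**The concern.** The study is observational, so an adjusted association between preoperative CMD-SQ and outcome is only as good as its confounder set. Within the shoulder group, operation and indication are free to vary. They could plausibly be related to the outcome scores and also to preoperative anxiety. If both relations exist, a model that adjusts only for co-morbidity and sociodemographic items will attribute some of the difference between operations to CMD-SQ.

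This is separate from the hip-versus-shoulder question. Splitting by joint, or adjusting for joint, leaves the mixture inside the shoulder group as it was.

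The Discussion says a confirmed hypothesis would lead to recommending preoperative screening of all hip and shoulder patients and would help select those likely to do well. A coefficient that partly stands for which operation was done would be a weaker basis for either step.

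**Working it through.** **Inputs from the documents.** The required number of shoulder patients is 202 (Sample size) and planned recruitment is 250. With the response of about 90% expected in the Discussion, 250 × 0.90 = 225, which exceeds 202. The 202 itself cannot be reproduced, because no alpha, power, effect size or SD is given. It serves here only as the sample size.

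**Inputs assumed.** The documents say nothing about how operation type relates to CMD-SQ or to outcome. Every effect size below is an assumption, as is the two-sided 5% level.

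**Scenario A: operation related to both CMD-SQ and outcome, no effect of CMD-SQ itself.**

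1. Take two equal-sized operation groups that differ by 0.5 within-group SD on both measures.
2. The between-group covariance is 0.25 × 0.5 × 0.5 = 0.0625. The total variance of each measure is 1 + 0.25 × 0.5² = 1.0625.
3. Spurious correlation = 0.0625 / 1.0625 = 0.059, about 0.06.
4. By Fisher's z with n = 202 and r = 0.06, the test statistic is shifted by atanh(0.06) × √199 = 0.847. Rejection probability = Φ(0.847 − 1.960) + Φ(−0.847 − 1.960) = 0.135, about 14% instead of 5%.

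The result depends on the assumed strengths. With spurious r = r(operation, CMD-SQ) × r(operation, outcome) and n = 202:

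| r(operation, CMD-SQ) | r(operation, outcome) | Spurious r | False positives |
|---|---|---|---|
| 0 | 0.3 | 0 | 5% |
| 0.1 | 0.3 | 0.03 | 7% |
| 0.2 | 0.3 | 0.06 | 14% |
| 0.3 | 0.3 | 0.09 | 25% |
| 0.3 | 0.5 | 0.15 | 57% |

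For scale, 202 patients give 80% power for r = tanh((1.960 + 0.842) / √199) = 0.196, about 0.20.

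**Scenario B: operation related to outcome only.** There is no bias. If operation explains a share R² of outcome variance, adjustment multiplies the standard error of the CMD-SQ coefficient by √(1 − R²):

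- R² = 0.10: √0.90 = 0.949, a cut of about 5%.
- R² = 0.20: √0.80 = 0.894, a cut of about 11%.

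These are upper limits, because age, co-morbidity or a baseline score in the model may already absorb part of that variance.

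**The two gains do not add.** In general the standard-error ratio is √[(1 − R² of outcome on operation) / (1 − R² of CMD-SQ on operation)]. In the 0.5 SD case of Scenario A, operation explains 0.0625 / 1.0625 = 5.9% of both measures, so the ratio is √(0.941 / 0.941) = 1. Adjustment there removes bias but gains no precision.

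**The case against.** The strongest case on the other side has five parts.

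1. **The heterogeneity sentence is weak evidence.** It stands in the section on co-morbidity and does not fit its own continuation. A reader might infer from it that the plan treats the shoulder group as surgically uniform. The documents do not support that: the sentence looks like a wording slip. The objection stands, and the point rests on the eligibility text and the confounder list instead.
2. **A condensed article is not an inventory of collected data.** A reader might infer that diagnosis and operation are not recorded at all, or that the problem cannot be repaired later. Neither can be shown. Study variables lists what enters the analysis, and operation codes could be taken from hospital records. What remains is the confounder set in Statistical analysis, itemised after *i.e.* and so a stated choice.
3. **The shoulder group is not wholly open.** Recent shoulder trauma, bone tumour and terminal status are excluded, and only first referrals enter. This is true, but none of these limits fixes the operation or indication.
4. **Timing.** The Discussion says "It is important to measure the patients when they are in a stable period because otherwise the outcome will be biased". A reader might infer that 12 weeks cannot be equally stable for every admitted operation. The article rests 12 and 52 weeks on cited studies that are not available here, so unequal stability would be conjecture and is not claimed.
5. **The aim is correlation and screening.** For screening all comers, the association across the actual case mix is relevant in its own right. That is fair, and it is a reason to show the association without operation type as well as with it. It does not settle the matter, because the plan itself undertakes to examine confounding.

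**Conclusion.** The point holds in a limited form. Shoulder eligibility names no operation or indication, the stated confounders contain neither, and separate analysis by joint would not remove mixing within the shoulder group. Whether bias follows is conditional: operation type must be related to both preoperative CMD-SQ and outcome after the listed covariates, and the documents give no evidence either way.

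On the assumed 0.5 SD case the distortion is small next to the detectable correlation (about 0.06 against 0.20), yet it nearly triples the false-positive rate, from 5% to about 14%. If operation is unrelated to CMD-SQ, only precision is at stake. The omission does not invalidate the study, but it leaves an obvious and easily obtained candidate confounder out of an analysis that depends on confounder control.

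**What to change.** - **Study variables:** add a procedure and indication group for the index operation, taken from the surgical record or from the National Patient Registry already used for the Charlson Index.
- **Statistical analysis:** add this group to the confounders and enter it as a factor in the shoulder regressions at both 12 and 52 weeks. Define the groups before modelling. Report the CMD-SQ association with and without it: the first addresses case mix, the second describes screening in the patients as they present.
- **Charlson Co-morbidity Index:** reword the heterogeneity sentence so that it says what was meant about co-morbidity and fits the shoulder definition under Population.

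The cost is one coded field per shoulder patient from existing records and a few degrees of freedom among about 200 patients. No extra recruitment or questionnaire is needed.

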#### Population

Patients scheduled for a total hip arthroplasty (THA).

This group represents a part of the adult population suffering from chronic pain. It has been shown that five to ten percent of these patients suffer from severe chronic pain postoperatively
[39].

Patients scheduled for a shoulder-operation.

This group was chosen because it constitutes a group of younger patients suffering from pain. Previously, they have been identified as a group who tend to develop anxiety and concern
[17].

#### Inclusion criteria

All hip- and shoulder-patients who are referred for the first time to the Department of Orthopaedic Surgery at Kolding Hospital, a part of Lillebaelt Hospital and the Department of Orthopaedics and Traumatology, Odense University Hospital, Denmark are included. The patients must be able to speak and read Danish and must be at least 18 years old. To be included, they must enter a patient programme that implies an operation.

#### Exclusion criteria

Patients with primary and secondary bone tumour or who are registered as terminal are excluded. Patients who have experienced a trauma against the shoulder within the past four weeks and those diagnosed with severe mental disorders such as schizophrenia, paranoid psychosis and bipolar affective disorders are excluded.

#### Sample size

A previous study showed a significant improvement in EQ-5D after both hip operations, THA’s and shoulder operations and based on these results, this study will include a total of 202 shoulder patients and 36 THA patients
[40]. This corroborates the sample size and power estimation of another study assessing OHS, SF-12 and EQ-5D at baseline and 12 months after an operation
[41]. There are no studies showing the results of CMD-SQ before and after an operation.

It will be possible to include 250 THA patients and 250 shoulder patients in a one-year inclusion period.

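### The stated sample-size basis, pre-to-post EQ-5D improvement, does not address the CMD-SQ association the study will test, so calling 202 required and the number sufficient is unsupported

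*Protocol article*

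**What the plan says.** All places are in the protocol article.

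- **Sample size, basis.** The starting point is an earlier study: "A previous study showed a significant improvement in EQ-5D after both hip operations", and likewise after shoulder surgery. From this the section concludes: "based on these results, this study will include a total of 202 shoulder patients and 36 THA patients". Support is claimed from a second study: "This corroborates the sample size and power estimation of another study assessing OHS, SF-12 and EQ-5D at baseline and 12 months after an operation". The section concedes: "There are no studies showing the results of CMD-SQ before and after an operation".
- **Sample size, recruitment.** The closing sentence reads: "It will be possible to include 250 THA patients and 250 shoulder patients in a one-year inclusion period". The Abstract (Methods/design) gives the matching total of 500.
- **Discussion.** On dropout: "Therefore, in order to get 202 patients (i.e. the required sample size) it is planned to include 250 patients". A response rate near 90% is then cited, "which makes our patient number sufficient as planned in the power calculation".
- **Aim and hypothesis; Statistical analysis.** The aim is a correlation between anxiety and concern on one side and perceived quality and outcome on the other. The main result is the correlation of CMD-SQ with SF-12, EQ-5D, OHS/OSS, RCS and HVOK. It is examined by multiple linear regression, once from baseline to 12 weeks and once from baseline to 52 weeks. The Charlson Index and seven sociodemographic variables are the candidate confounders.

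**The concern.** The only basis given for 202 and 36 is how much EQ-5D improves from before to after surgery. That is a mean change within patients. The planned analysis estimates a slope: do patients with higher CMD-SQ scores report worse outcome or lower satisfaction than others? Surgery can raise everyone's EQ-5D greatly while CMD-SQ explains none of the variation, and the reverse is equally possible. No aim or hypothesis concerns mean EQ-5D change, and EQ-5D is only one of five secondary instruments. The supporting study is also described as a baseline-to-12-month assessment, so it does not close the gap.

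The Discussion nevertheless makes a positive claim of adequacy. That claim will govern how a null result is read: told that the number was sufficient, a reader may take a null to mean no relevant association, although nothing in the article says which association the study could have detected.

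The numbers also do not fit together. The Sample size section says the study will include 202 shoulder and 36 hip patients, 238 in all, and then plans 250 of each. The step from 202 to 250 is explained by dropout. The step from 36 to 250 is not explained.

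**Working it through.** **1. Can 202 and 36 be reproduced?** No. The article gives no mean change, SD, alpha or power. One can only ask what paired change each number would match. Assuming two-sided 5% and 80% power, (1.960 + 0.842)/√n gives:

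- n = 202: 2.802/14.21 = 0.20 SD
- n = 36: 2.802/6 = 0.47 SD

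This is consistent with pre/post sizing but does not prove it, since any n can be solved back to some effect. The evidence for the basis is the section's wording.

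**2. How many will be analysed?** Inputs from the article: 250 per joint and about 90% response.

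- 250 × 0.90 = 225 per joint; both joints together, 450.
- Going from 202 to 250 allows for 1 − 202/250 = 19.2% loss. At 10% loss, 202/0.90 rounds up to 225, so 250 covers the stated response rate.
- If 90% applied independently to both baseline and one follow-up: 250 × 0.90² = 202.5.

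**3. What can the planned regression detect?** For one slope adjusted for k covariates, by Fisher's z:

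r = tanh[(z for alpha + z for power)/√(n − 3 − k)]

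Here k = 8 (Charlson Index plus gender, age, weight, height, citizenship, civil status and education, each counted once). Alpha and power are assumptions.

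| Analysed | Two-sided alpha | Calculation | Detectable partial r, 80% power |
|---|---|---|---|
| 202 (one joint) | 0.05 | tanh(2.802/√191) | 0.20 |
| 225 (one joint) | 0.05 | tanh(2.802/√214) | 0.19 |
| 450 (pooled) | 0.05 | tanh(2.802/√439) | 0.13 |
| 225 (one joint) | 0.005 | tanh(3.649/√214) | 0.24 |

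The last row divides 0.05 by 5 outcomes × 2 time points = 10. The article does not specify such a split; the row shows how sensitive the figure is to it. With 12 covariate terms (an assumption, if categories are dummy coded), the results at two-sided 5% are 0.202 at n = 202 and 0.191 at n = 225, so the number of terms hardly matters.

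**4. What would a null result exclude?** Power at two-sided 5% with 8 covariates:

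| True partial r | n = 202 | n = 225 |
|---|---|---|
| 0.10 | 28% | 31% |
| 0.15 | 55% | 60% |
| 0.20 | 80% | 84% |
| 0.30 | 99% | 99.5% |

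A null per joint would speak against r of 0.20 or more with reasonable confidence. It would say little about r of 0.10 to 0.15.

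**The case against.** The strongest reply is that the planned enrolment is adequate anyway. With 225 per joint, power at r = 0.20 is 84% with 8 covariates, and the Discussion links 202 to 250 through dropout. This stands. The defect lies in the justification, not in a demonstrated shortage of patients.

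It can also be said that a condensed article need not give alpha, power or effect size. That stands too, and their absence is not the complaint. The complaint is that the basis the article does give belongs to another question, and that sufficiency is asserted on it.

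Four stronger readings are tempting but not supported:

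- *The study is underpowered.* The documents name no smallest association of interest, so insufficiency cannot be shown. Power is limited only for weak associations or under strict multiplicity control.
- *Only 36 hip patients will be studied.* With 36, the detectable r would be about 0.51 (8 covariates), but 250 hip patients are planned. The 36 is a textual conflict, not the size of the hip analysis.
- *Attrition takes the number below 202.* Compounding 90% over three or four waves gives 182 or 164. That requires a per-wave rate, independent losses and complete data at every wave. The Discussion does say that the study depends on four completed questionnaires, but each regression in Statistical analysis uses baseline plus one follow-up. Even the harsher two-wave figure is 202.5.
- *202 was in fact derived for the regression.* It happens to equal the number needed for partial r = 0.20 with 8 covariates at 80% power. Nothing in the article says it arose that way; the text attributes it to EQ-5D improvement.

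**Conclusion.** The concern holds as a mismatch between the stated basis and the planned analysis. Improvement in EQ-5D cannot make 202 the required number for a CMD-SQ association, and it cannot make the number sufficient for one. Both statements in the Discussion are unsupported for the regression. Separately, announcing 202 + 36 conflicts with planning 250 + 250, and the hip figure is left unexplained.

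On size: at two-sided 5%, 80% power and 8 covariates, the study can detect a partial r of about 0.19 to 0.20 per joint (225 to 202 analysed). This becomes about 0.13 if the joints are pooled, and about 0.24 at 225 if alpha is divided by ten. Alpha, power, the alpha split and one term per covariate are assumptions. Whether the joints are pooled is not settled by the article: it says the analyses are done separately, but not that this means by joint. What changes is the claim that can be attached to a null result, not enrolment or conduct.

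**What to change.** In the Sample size section:

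- Delete the derivation from EQ-5D improvement, the supporting sentence about the second study, and the figure of 36 hip patients.
- State that 250 per joint is set by what can be recruited in one year.
- Give the association detectable at the expected number analysed, with alpha, power and number of covariates. On the assumptions above: partial r of about 0.19 at 225 per joint (0.20 at about 202), or about 0.13 if the joints are pooled at 450. Say which of the two applies.
- Note that the figure rises to about 0.24 at 225 if alpha is split over five outcomes and two time points.

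In the Discussion, stop calling 202 required and replace the sufficiency claim with the same figure. If the investigators can name the smallest association that would matter for screening, setting it beside the detectable one would make a null result easier to read.

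The cost is one rewritten paragraph and one changed sentence. No extra patients, data or analyses are needed. The price is a less favourable but explicit statement of what the study can detect.
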